**Fig. 1 Fig1:**
[figure not shown]
Overview of study procedure

### Baseline characteristics and in-hospital data

The following data will be collected preoperatively: main diagnosis and secondary diagnoses, sex, age, marital status, education, and professional qualification. During the operative procedure, medication-related variables (e.g., analgesics, muscle relaxants, antiarrhythmics, and PONV), transfusions, infusions, diuresis, lactate values, and hemoglobin values as well as values from the electrocardiogram and the cardiopulmonary bypass will be gathered. Furthermore, all clinically relevant events, the results of diagnostic procedures, medication (e.g., analgesics, antiemetics), the intensity of pain, PONV, dizziness, or delirium, as well as nursing procedures and physiotherapeutic/psychosomatic interventions during the in-hospital stay will be recorded. In addition, adverse events and serious adverse events respectively as well as all dropouts during the whole study period will be captured.

### Outcomes

#### Primary outcomes

Two indicators are set as co-primary endpoints, while both a priori null hypotheses must be rejected for reaching the study success:Total days in hospital due to cardiac causes (including the initial in-hospital stay for surgery) during the first postoperative yearFunctional performance measured by the 6MWT [22] at the time point of hospital discharge

#### Secondary outcomes

Several secondary outcome measures will be used. See Table 1 for an overview of the different measurement time points for specific assessments.Goal Attainment Scale (GAS) [23] for determination and assessment of individualized participants’ goals in the intervention group at discharge (short-term goal), after 3 months (intermediate goal), and after 12 months (long-term goal)German version [24] of the HeartQoL [25] measuring health-related quality of life, especially in patients with heart diseaseGerman version [26] of the 5-level EQ-5D health-related quality of life questionnaire (EQ-5D-5L) [27]German version [28] of the Brief Illness Perception Questionnaire (BIPQ) [29] for assessment of individualized illness conceptionsSomatic Symptom Scale—8 (SSS-8) [30] for the measurement of somatic symptom burdenSomatic Symptom Disorder—B Criteria Scale (SSD-12) [31] to evaluate the dealing with somatic symptomsGerman version [32] of the Cardiac Anxiety Questionnaire (CAQ) [33] for quantitative assessment of cardiac anxietyPatient Health Questionnaire-9 (PHQ-9) [34] for the assessment of depression severityGeneralized Anxiety Disorder 2-item version (GAD-2) [35] for the measurement of anxiety severityGerman version [36] of the Life Orientation Test—revised (LOT-R) [37] to assess the dispositional optimismGerman version [38] of the International Physical Activity Questionnaire Short Form (IPAQ-SF) [39] to evaluate the level of physical activity6MWT to quantify the functional performance at 12 months postoperativelyTimed Up and Go (TUG) [40] to capture the functional performanceOne Minute Sit to Stand Test (1STS) [41] for the evaluation of physical performanceDynamometry to rate the hand grip [42]European Health Literacy Questionnaire HLS-EU-Q16 [43] to measure health literacyTreatment Expectation Questionnaire (TEX-Q) [44] to assess treatment expectationsGerman version [45] of the short form of the Readiness for Hospital Discharge Scale (RHDS) [46] for the assessment of readiness for hospital dischargeQuestionnaire for Health-Related Resource Use in an Elderly Population [Fragebogen zur Inanspruchname medizinischer und nicht-medizinischer Versorgungsleistungen im Alter] (FIMA) [47] to evaluate the use of health care services

**Table 1 Tab1:**
[figure not shown]
Schedule of enrolment, interventions, and assessments

*1STS* One Minute Sit to Stand Test, *6MWT* Six Minute Walk Test, *BIPQ* Brief Illness Perception Questionnaire, *CAQ* Cardiac Anxiety Questionnaire, *EQ-5D-5L* European Quality of Life 5 Dimensions 5 Level Version, *FIMA* Questionnaire for Health-Related Resource Use in an Elderly Population, *GAD-2* Generalized Anxiety Disorder-2, *GAS* Goal Attainment Scale, *HLS-EU-Q16* European Health Literacy Questionnaire, *IPAQ-SF* International Physical Activity Questionnaire Short Form, *LOT-R* Life Orientation Test –revised, *PHQ-9* Patient Health Questionnaire-9, *QoL* Quality of life, *RHDS* Readiness for Hospital Discharge, *SSD-12* Somatic Symptom Disorder – B Criteria Scale, *SSS-8* Somatic Symptom Scale-8, *TEX-Q* Treatment Expectation Questionnaire, *TUG* Timed Up and Go Test

### Data analysis

Data collection, processing, and storage will be according to valid regulations. Data will be entered by study nurses not involved in patient care and investigators ensuring principle of dual control must verify all data. An independent monitoring committee will review trial progress, will provide advice, and will supervise the trial including data integrity and safety. Statisticians not involved in the provision of care and blinded to the participants will perform analysis. Descriptives of the baseline and follow-up data will be presented in the whole study cohort as well as separately, according to the intervention and control groups. The type of presentation is defined by the scale of corresponding variable. For categorical variables, absolute and relative frequencies will be given. Median and interquartile range will be set for variables with ordinal scaling and a sufficient number of categories as well as for metric non-normally distributed variables. For metric normally distributed variables, the arithmetic mean and standard deviation will be presented. Descriptive *p*-values will be reported with respect to the baseline comparisons.

For both co-primary endpoints, two-factorial ANOVA models will be calculated, including the treatment group and study center as co-variates. From these models, the one-sided 97.5% confidence intervals for the mean differences will be calculated (for the hospital LOS assuming unequal variances, for the 6MWT assuming equal variances).

The absolute scale (i.e., mean total days in hospital in the intervention group minus mean total days in hospital in the control group) will be used for the first endpoint, while the relative scale ((mean 6MWT distance in the study group minus mean 6MWT distance in the control group) divided by the mean 6MWT distance in the control group) will be used for the definition of the 6MWT study co-endpoint. Thus, for the total days in hospital, negative values will indicate fewer days in hospital when receiving ERAS intervention; for the 6MWT walking distance, positive values will indicate longer walking distance in the ERAS intervention group. Accordingly, the null hypothesis regarding total days in hospital will be rejected when the upper limit of the associated confidence interval will be below zero. The null hypothesis regarding walking distance in the 6MWT will be rejected if the lower limit of the associated confidence interval will be above -0.15 (non-inferiority limit).

The intention-to-treat analysis will be performed. Additionally, the data will also be analyzed using a per protocol approach. No interim evaluations are scheduled.

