### Sample and recruitment

Study subjects will be equally recruited at the University Medical Center Hamburg-Eppendorf and at the University Hospital Augsburg, both Germany. All patients scheduled for minimally invasive heart valve surgery (i.e., mitral valve or aortic valve surgery) as primary inclusion criteria will be contacted by screening call and the study objectives will be introduced. If patients are keen to participate and give their formal consent, a final eligibility screening is conducted. During this final screening assessment, the study-specific inclusion and exclusion criteria will be verified. Inclusion criteria are as follows:Indication for elective minimally invasive aortic or mitral valve surgeryAbility to adequately understand the nature and extent of the individual's requirements for participation in the ERAS model of careWritten informed consentFunctional status classification as “FIT” or “Pre-FRAIL” with the LUCAS functional index derived from the Longitudinal Urban Cohort Ageing Study (LUCAS) [18]

Patients will be excluded if they had one of the following conditions or co-morbidities at baseline:Severe chronic obstructive pulmonary disease (GOLD III or IV)Dialysis-dependent renal failureAdvanced liver cirrhosis (Child stages B + C)Residual neurological impairment after prior stroke, especially leg-related hemiplegia, major restrictions of mobility, and/or neuropsychological disordersPredicted life expectancy < 1 year (e.g., advanced malignancy)Previous cardiac surgery (i.e., relative contraindication for minimally invasive technique)Severe depressive disorderSubstance-related addictive disorders (e.g., alcohol, drugs)Lack of a social environment that ensures an adequate supportive care during perioperative course

If patients are eligible to participate, they will receive in-detail study information via telephone and by post. Potential participants will have the opportunity to ask questions directly during the telephone call or at any time later on via email, telephone, or personal contact depending on their personal preference. After the screened candidates confirm their willingness to participate, they will sign the written informed consent.

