### Sample size calculation

Sample size calculation is based on the two co-primary endpoints: (a) total days in hospital due to cardiac causes during the first postoperative year and (b) physical performance measured by the Six-Minute Walk Test (6MWT). For the first primary co-endpoint, a superiority hypothesis was established expecting the hospitalization time in the intervention group to be shorter than in the control group. Regarding the second primary co-endpoint, a non-inferiority hypothesis is assumed stating that participants in the intervention group, although being discharged earlier, will achieve comparable values to the control group in the physical performance measurement. For the study success, both primary null hypotheses must be rejected.

Because these are co-primary endpoints, adjustment of the type I error for multiple testing is not required. Type I error is fixed at *α* = 0.025 based on the one-sided test. However, because the power is affected by the chosen study design, it is set to 90% for the single hypotheses to ensure an overall power of at least 80%.

In terms of superiority hypothesis, no precise data are available regarding in-hospital days for cardiac reasons during the first year after surgery. Nonetheless, we assume that the total number of in-hospital days does not differ between both groups after initial discharge after surgery. Therefore, the mean primary in-hospital stay served as a background for sample size calculation. For this purpose, we used the data derived from internal evaluation of the University Medical Centre Hamburg-Eppendorf during the pilot phase of ERAS program. The mean LOS was 6.1 days with a standard deviation (SD) of 2.5 days in the intervention group, as compared to 8.0 days with an SD of 4.1 days in the control group. Using the two-sample *t* test based on unequal variances, the sample size needed to demonstrate the superiority in the intervention group was 69 patients per group, or 138 patients in total.

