### Randomization and blinding

Patients will be randomized (1:1) after written informed consent and study inclusion prior to any treatment arm-specific intervention. Central block randomization with variable block length will be used. Randomization will be stratified by the institution of treatment. Since no prognostically relevant variables are known in the included patient population, no further variables will be stratified for at randomization.

The randomization codes will be generated by a biostatistician using a random number generator. A third person not involved in the randomization process will prepare opaque sealed envelopes containing the participant’s order on the outside and the participant’s group allocation on the inside. Study nurses in both study centers will open the envelopes in the designated order to allocate the participants. Thus, the nondisclosure of the group allocation will be ensured.

Blinding of the participants and health care professionals will not be possible due to the different interventions in both study groups. Blinding of the assessors of the performance measurements will also not be possible due to the different time points of measurements; however, the assessors will not be involved in the treatment process in the two groups. The statistical analysis of the study data will be performed by blinded statisticians.

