### Control group

Having an indication for elective minimally invasive aortic or mitral valve surgery, all participants need to be treated; hence, an active comparator as control group was chosen. The control group receive the treatment as usual (TAU) according to the established standards in the two study sites and depending on individual needs. In contrast to the intervention group, they will not receive an outpatient educational session prior to admission and will be transferred intubated to the intensive care unit (ICU) instead of being transferred to the specialized PACU. These patients receive only routine physiotherapy according to the standard of care that is one visit at the intensive care unit and one visit at normal ward, unless individual indications are present. Furthermore, no psychosomatic support and counseling by an INCREASE nurse will be included.

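### Both co-primary models adjust for centre only; prespecifying age, sex, valve position and LUCAS class would gain some precision at almost no cost

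*Protocol article*

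**What the plan says.** Under Data analysis, for both co-primary endpoints, "two-factorial ANOVA models will be calculated, including the treatment group and study center as co-variates". One-sided 97.5% confidence intervals come from these models, with unequal variances for hospital days and equal variances for the walk test. Hospital days are compared on the absolute scale. The walk test is compared on the relative scale, against a limit of -0.15. The section gives no reason for its choice of covariates.

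Under Randomization and blinding, "Randomization will be stratified by the institution of treatment". The article then explains why it goes no further: "Since no prognostically relevant variables are known in the included patient population, no further variables will be stratified for at randomization".

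Several patient-level variables are available before treatment. Baseline characteristics and in-hospital data lists, as collected preoperatively, "main diagnosis and secondary diagnoses, sex, age, marital status, education, and professional qualification". Sample and recruitment requires classification as FIT or Pre-FRAIL "with the LUCAS functional index derived from the Longitudinal Urban Cohort Ageing Study". All participants have an "indication for elective minimally invasive aortic or mitral valve surgery", so valve position is known at inclusion.

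**The concern.** The included population is heterogeneous in ways that could plausibly affect walking distance and hospital stay. It spans two functional classes and a range of ages. It also spans two operations through different incisions: Intraoperative components describes a right anterolateral approach for the mitral valve and a partial upper sternotomy for the aortic valve. If these variables predict either endpoint, leaving them out of the model keeps explainable variance in the residual and makes both intervals wider than necessary.

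Both null hypotheses must be rejected for the trial to succeed, so precision matters on each endpoint. With 84 evaluable patients per arm, a chance imbalance in a predictive factor would shift the estimate. The interval allows for such shifts, but adjustment would reduce them. The covariates have to be named in advance, because a set chosen after seeing baseline differences carries little weight.

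The statement that no prognostic variables are known also sits uneasily with a protocol that selects patients on functional status and has a functional test as a co-primary endpoint.

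**Working it through.** **Inputs from the article (Sample size calculation).** The type I error is "0.025 based on the one-sided test" and power is 90% per hypothesis. Length of stay: means 6.1 and 8.0 days, SDs 2.5 and 4.1, difference 1.9. Walk test: mean 300 m, SD 89 m, margin 45 m, true difference 0. **Assumed, not in the article:** R² of the four covariates for either endpoint, taken from 0 to 0.30.

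**Step 1: reproduce the plan's figures (noncentral t).**
- Length of stay, 69 per arm, Welch test: SE = √((2.5² + 4.1²)/69) = 0.578; 1.9/0.578 = 3.29; power 0.903. With 68 per arm it is 0.899, so 69 is right.
- Walk test, 84 per arm, equal variances: SE = 89·√(2/84) = 13.73 m; 45/13.73 = 3.28; power 0.903. With 83 per arm it is 0.899, so 84 is right.
- Length of stay at 84 per arm: SE = √(23.06/84) = 0.524; 1.9/0.524 = 3.63; power 0.950.
- Treating the endpoints as independent, 0.903 × 0.950 ≈ 0.86, above the stated 80%.

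The plan therefore reaches its target without covariates.

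**Step 2: effect of covariates on the standard error.** Residual SD = SD·√(1 − R²), so the SE shrinks by the factor √(1 − R²). The four covariates use four degrees of freedom. With 168 patients the residual degrees of freedom go from 165 to 161, which does not affect power to the precision shown.

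**Step 3: walk test on the absolute scale.** Noncentrality = 45/(89·√(1 − R²)·√(2/84)).

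**Step 4: walk test on the relative scale.** This is what Data analysis actually tests. If the interval allows for the estimated control mean, the hypothesis is (intervention mean − 0.85 × control mean) > 0. At equal means of 300 m the distance is 300 − 255 = 45 m, and SE = 89·√((1 + 0.85²)/84) = 12.74 m, so 45/12.74 = 3.53 and power is 0.939 before any adjustment. Scaling this SE by √(1 − R²) is an approximation for adjusted means.

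| Assumed R² | SE reduction | Walk test power, absolute | Walk test power, relative | Hospital-days power (index-stay SDs) | Walk test n per arm for 90% (absolute) |
|---|---|---|---|---|---|
| 0 | 0% | 0.903 | 0.939 | 0.950 | 84 |
| 0.05 | 2.5% | 0.917 | 0.950 | 0.959 | 80 |
| 0.10 | 5.1% | 0.930 | 0.959 | 0.967 | 75 |
| 0.20 | 10.6% | 0.954 | 0.975 | 0.981 | 67 |
| 0.30 | 16.3% | 0.973 | 0.987 | 0.990 | 59 |

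On the absolute scale the 95% half-width for the walk test narrows from 1.96 × 13.73 = 26.9 m to 22.5 m at R² = 0.30.

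**Step 5: which covariates qualify.** Age and sex are fixed characteristics. The valve indication and LUCAS class are settled at eligibility, before randomisation. Baseline walk distance would be the obvious further candidate, but Time points of measurements places t0 just before the educational session (2 to 4 weeks before surgery) in the intervention arm and on the first hospital day in the control arm. A baseline measured at different times by arm should not enter the primary model.

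**The case against.** The strongest reply is that nothing is wrong with the planned analysis. It includes the only stratification factor, it is valid and unbiased under randomisation, it broadly matches the t-test basis of the sample size, and it meets the stated power. Chance imbalance is already reflected in the confidence interval. All of this stands, and it is why the point is about efficiency only.

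A second reply is that the gain is hypothetical. The article gives no R², LUCAS class is restricted to two levels, and on the relative scale the improvement is smaller. This also stands. At R² = 0.05 the absolute-scale gain is 1.4 points, and near zero there is none. The hospital-days column applies the same assumed R² and is not evidence that these variables predict hospital days.

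A third reply is that supportive adjusted analyses may be in an analysis plan that is not shown. That may be so, but the article does fix the model for the primary inference.

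Three stronger readings are tempting and are not supported:
- A reader might infer that the models omit covariates because no prognostic variables are known. The article offers "Since no prognostically relevant variables are known in the included patient population" only as the reason for not stratifying further.
- A reader might see a flat contradiction with the LUCAS criterion. The article does not say why it screens on LUCAS, and the remark is limited to an already narrowed population. The wording is loose, not contradictory.
- A reader might expect adjustment to make good any power lost to readmission days, which the sample size does not model. Nothing in the article shows that these four variables predict those days.

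**Conclusion.** The point holds as a recommended improvement. Both co-primary models are fixed with treatment and centre only, while four usable covariates are available before treatment. The size cannot be pinned down from the article: under an assumed R² of 0 to 0.30, walk-test power at 84 per arm rises by 0 to 7.0 percentage points on the absolute test (0.973 − 0.903) and by 0 to 4.8 on the relative test (0.987 − 0.939). These figures rest on the article's SD of 89 m, no true difference and full evaluability of 168 patients. The stated sample sizes need no change.

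**What to change.** Prespecify, in both co-primary models, treatment, centre, age, sex, valve position as indicated at inclusion (aortic or mitral) and LUCAS class (FIT or Pre-FRAIL). In addition:
- Keep an unequal-variance (robust) standard error for hospital days.
- Define the relative walk difference from the covariate-adjusted means, with an interval that allows for the estimated adjusted control mean in the denominator.
- Report the centre-only model as a sensitivity analysis.
- Do not use t0 walk distance as a primary covariate.
- Under Randomization and blinding, soften the remark on prognostic variables, for example by saying that stratification was limited to centre to keep the scheme simple, if that was the reason.

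The cost is four degrees of freedom, the wording of the model, and a definition of the adjusted control mean. No new measurements are needed, provided the LUCAS class and valve indication from screening are carried into the analysis data.

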Regarding the non-inferiority hypothesis on the physical performance between the study groups, a mean walking distance of 300 meters with an SD of 89 meters is assumed for the standard surgical procedure [19]. These results are also expected for the intervention group. A deviation > 15 percentage (i.e., > 45 m) was defined as relevant (non-inferiority boundary), based on clinical considerations. Using the two-sample *t*-test based on equal variances, the number of cases to prove the non-inferiority was 84 patients per group, or 168 patients in total.

Thus, to successfully complete the study, a total of 168 patients (maximum of the two case numbers) are required. To compensate for possible dropouts, additional 10% (*n* = 16.8 ≈ 18) participants were calculated. This final adjustment results in a total subject number of *N* = 186 (*n* = 93 per treatment arm).

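### The 6MWT non-inferiority test is decided on a relative scale, but the only interval named is for a mean difference; rescaling it would give a conservative test, and the stated power belongs to a different rule

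*Protocol article*

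**What the plan says.** Sample size calculation (protocol article) gives the planning values: "a mean walking distance of 300 meters with an SD of 89 meters is assumed for the standard surgical procedure", and "These results are also expected for the intervention group". The margin is stated first as a percentage and then in metres: "A deviation > 15 percentage (i.e., > 45 m) was defined as relevant (non-inferiority boundary), based on clinical considerations". An equal-variance two-sample t-test is applied, and "the number of cases to prove the non-inferiority was 84 patients per group". The error rate and power are set by "Type I error is fixed at *α* = 0.025 based on the one-sided test" and "it is set to 90% for the single hypotheses to ensure an overall power of at least 80"%.

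Data analysis (protocol article) specifies a two-factor ANOVA with treatment and centre, from which "the one-sided 97.5% confidence intervals for the mean differences will be calculated", with equal variances assumed for the 6MWT. The 6MWT effect is then defined as the difference in means divided by the control mean, and the null hypothesis is rejected if "the lower limit of the associated confidence interval will be above -0.15 (non-inferiority limit". The section does not say how an interval in metres becomes an interval for a ratio of two estimated means.

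**The concern.** Three elements are fixed and do not fit together: a sample size computed for a fixed 45 m difference, an interval for a difference in metres, and a decision limit without units. The simplest way to join the last two is to divide the lower limit in metres by the observed control mean. That treats an estimated denominator as a known constant.

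What matters for the relative hypothesis is the variability of mean_T − 0.85·mean_C, whose variance is σ²(1 + 0.85²)/n. The named interval carries 2σ²/n instead. Its error rate would then not be the nominal one, and in either reading the 90% power was computed for a rule other than the one applied. Both co-primary null hypotheses must be rejected for the trial to succeed, so this test alone can decide the result.

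**Working it through.** **Inputs from the protocol article.** One-sided α = 0.025; power 90% per hypothesis; control mean 300 m; SD 89 m in both arms; true difference 0; margin 15% = 45 m; n = 84 per arm. With df = 2·84 − 2 = 166, the critical value is t = 1.974. The centre term is left out throughout.

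**Step 1: reproduce the stated sample size (fixed 45 m).**
SE = 89·√(2/84) = 13.73 m; noncentrality = 45/13.73 = 3.277. Noncentral-t power is 90.3% at 84 per arm and 89.9% at 83. The stated 84 is right for a fixed 45 m difference.

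**Step 2: ratio-scale test.**
H0: mu_T ≤ 0.85·mu_C. Statistic: (mean_T − 0.85·mean_C) / [s·√((1 + 0.85²)/n)], with 1 + 0.85² = 1.7225.
SE = 89·√(1.7225/84) = 12.74 m. With equal true means of 300 m the contrast is 0.15·300 = 45 m, so the noncentrality is 45/12.74 = 3.53.
- Type I error: 2.5%.
- Power at 84 per arm: about 94%.
- n for 90% power: 72 per arm.

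**Step 3: mean-difference limit divided by the observed control mean.**
The rule [mean_T − mean_C − t·s·√(2/n)] / mean_C > −0.15 rearranges, for a positive control mean, to mean_T − 0.85·mean_C > t·s·√(2/n). This is the contrast of Step 2 with a critical value too large by √(2/1.7225) = 1.0775, that is 1.974·1.0775 = 2.127.
- Type I error at the margin: P(t₁₆₆ > 2.127) = 1.74%.
- Power at 84 per arm: 91.9%.
- n for 90% power: 79 per arm.

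Simulation at 300 m (50,000 trials per scenario) gave type I error 2.47% and 1.73%, and power 94.0% and 91.9%, for Steps 2 and 3 respectively.

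**Step 4: dependence on the control mean.** Control means other than 300 m are assumptions, because the document gives no other value. SD is held at 89 m, n is 84 per arm, and the true means are equal.

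| Control mean | 15% in metres | Power, ratio test | Power, rescaled interval |
|---|---|---|---|
| 250 m | 37.5 | 83.3% | 79.2% |
| 275 m | 41.25 | 89.6% | 86.5% |
| 300 m | 45 | about 94% | 91.9% |
| 325 m | 48.75 | 96.7% | 95.4% |
| 350 m | 52.5 | 98.4% | 97.6% |
| 400 m | 60 | 99.7% | 99.5% |

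Power drops below 90% for a control mean under about 277 m (ratio test) or about 291 m (rescaled interval). A fixed 45 m rule would stay at 90.3% throughout, which is why the planning calculation does not reveal this dependence.

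**The case against.** The margin itself is consistent. The sample size section states it as 15% first, 45 m is 15% of the assumed 300 m, and the decision rule again uses 15%. Planning a relative margin at an assumed control mean is ordinary practice. This stands: a reader might infer two contradictory margins, but the document does not contain them.

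A reader might also infer that the two scales could give opposite verdicts on the same data, for example if controls walked 360 m. That compares the stated rule with a 45 m decision rule that no section applies. At 360 m a true 45 m deficit is 45/360 = 12.5%, inside the 15% margin, so declaring non-inferiority there would not be a false positive.

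No sentence says that the mean-difference limit is to be divided by the control mean. The associated interval could be read as one for the relative endpoint, with the method left to an analysis plan not shown here. This stands in part: the 1.7% depends on the rescaling reading, and with a proper ratio interval the error rate is exactly 2.5%. It does not dispose of the point, because the article does not leave the interval open. It names the model, the type of interval, the variance assumption and the limit, and the named interval has the wrong width for the stated rule.

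The power range in Step 4 also depends on holding the SD at 89 m. If the SD scaled with the mean, ratio-test power would stay at about 94% for every control mean.

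**Conclusion.** The point holds in a limited form and should be fixed. The interval named for the 6MWT does not match the relative decision rule, and the 90% power was computed for a fixed 45 m difference that treats the 300 m control mean as known.

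At the protocol's own assumptions, the rescaled interval costs about 0.8 percentage points of type I error (1.7% against 2.5%) and about 2 points of power (92% against 94%). The error is nominal or conservative under either reading and never inflated against the 15% null. The document does not support calling the trial undersized: power exceeds 90% both ways at 300 m, and 84 per arm covers the 72 or 79 needed. The remaining exposure is loss of power, and a tighter margin in metres, if control patients walk well under 300 m. That exposure rests on assumed control means and a constant SD.

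**What to change.** Keep the relative margin. For the 6MWT, replace the mean-difference interval by a test of the contrast mu_T − 0.85·mu_C > 0 at one-sided 2.5%, using the centre-adjusted means from the ANOVA already planned. Equivalently, require the one-sided 97.5% Fieller lower limit for the relative difference to exceed −0.15.

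Restate the 6MWT power for that rule as about 94% at 84 per arm (control mean 300 m, SD 89 m). Add a short table over assumed control means, for example about 83% at 250 m and above 99% at 400 m with SD held at 89 m, and state the SD assumption.

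The cost is a change of wording in the protocol or analysis plan and one line of code, settled before treatment groups are unblinded to the statisticians. The sample size does not change.
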